#### Parent meeting

The information-based interactive parent meeting will be 45 min and will take place in August-September 2023, i.e., shortly after the start of the 1st semester. Parents from one/a couple of classes (depending on the size of the school and feasibility) will be invited to attend the meeting. The meeting is physical (in person) and takes place the same day as the schools’ own information meetings for parents. It will entail a 15-minute presentation emphasizing the important role of parents in supporting their adolescents and helping them navigate the challenges related to this developmental period and to starting high school. Parents will be offered concrete, research informed advice about how they can reduce risk of hazardous substance use and promote well-being. To address that culturally, many Danish parents do not see adolescent high intensity drinking as harmful, parents are also informed about practical, real-world frequently reported consequences such as intimate contact or sex that is later regretted; arguments or fights; and increased risk of use of nicotine products and illegal substances. Following the presentation, the group leader facilitates a discussion and exchange of experience between parents based on prepared questions (approximately 30 min). After the meeting, parents will be given a summary of the information to take home (in leaflets).

#### Structural + group MI condition

The structural + group MI condition consists of the elements described above and group MI. Within school classes randomized to receive group MI, participants will be divided into groups with 6–9 participants in each group (depending on class size). The size of the groups is in line with previous clinical trials of group MI by this team [74, 83, 84] including our recent pilot study [67]. Delivering the intervention to all students universally regardless of youth’s individual alcohol use, has several benefits, including maximal reach for the range of adolescent drinking and avoiding inadvertent stigmatizing of adolescents already engaged in drinking.

In Danish high schools, students start in an introductory class in August and change to a permanent class at the beginning of November in the first school year based on choice of study program. Group MI will be delivered in November-December 2023, i.e., after the students start in their permanent class.

The intervention is manualized [85] and consists of two one-hour group sessions administered over two consecutive weeks. The first session is focused on “Tell your story”, “Gains from not drinking”, and “Social norms.” In the second session, focus is on “Personal values”, “Linking values with behavior” and “Planning/choices regarding alcohol”.

Following our recent pilot study [67], the group MI intervention sessions will take place in a classroom at the target schools during the school day. Group MI sessions will be delivered by study staff, trained in group MI. All sessions will be audio-recorded via a digital recorder to ensure MI fidelity and to avoid therapist drift.

### Sample size

Sample size planning was done using simulation in Stata version 17 [86]. Specifically, four level nested data were simulated – levels were repeated measurements (level 1) nested within students (level 2) nested within school classes (level 3) nested within school (level 4). The simulation uniform randomly varied (1) school size between 2 and 11 school classes, and (2) school class size between 25 and 28 students. Random effects for student, school class, and school as well as residual for repeated measurements were randomly sampled from normal distributions with mean zero and variances specified at different values. 33% of sampled schools were assigned to the control condition, whereas school classes in the remaining 66% of sampled schools were assigned 50/50 to either structural only intervention or structural + group MI intervention. The above combined with á priori specified trajectories of alcohol consumption across the four measurements in the three conditions (control, structural only, structural + group MI) were finally aggregated to form the outcome analyzed for power estimation. The simulated outcome was truncated at zero, i.e., if specific simulated outcome was below zero (i.e., indicating “negative number of consumed alcohol units”), the simulated outcome was set to zero.

Finally, to estimate power the above simulated outcomes were analyzed using four-level mixed linear models with random intercept and with interaction between experimental condition and measurement timepoint to allow for different developmental trajectories across the three conditions. Parameters were estimated using restricted maximum likelihood, and for each estimated model, three parameters were tested for significance at alpha = 0.05. The three parameters tested were: 12 months follow-up difference between (1) control and structural only, (2) control and structural + group MI, and (3) structural only and structural + group MI. For a specific set of simulation parameters (i.e., number of sampled schools, variance of random effects and residual, and trajectories of alcohol consumption in each of the three conditions) simulation based power for testing each of the three parameters were estimated as proportion of 1000 estimated models where the specific parameter was statistically significant at alpha = 0.05.

Sufficient power of > 0.80 was reached when including 15 schools assuming 12 months follow-up difference in alcohol consumption (primary outcome) between control condition and structural only condition was 1.5, and between control condition and structural + group MI condition was 3.5, and between structural only condition and structural + group MI condition was 2.0 (further assuming variance of school level = 2, variance at school class level = 2, variance at individual level = 4, and variance of residual = 7).

### Assignment of interventions

[name] generated the allocation sequences via computer generated random numbers in Stata version 17 [86]. First, allocation sequence at school level was randomly generated using uniformly random block sizes of 3 or 6 schools, with 33% of schools allocated to control condition and 66% of schools allocated to intervention condition (Spring 2023). Second, within each school allocated to intervention condition, 50% of school classes will be randomly allocated to the structural only condition and 50% will be randomly allocated to the structural + group MI condition. If a school has an uneven number of school classes, random allocation to intervention-type will be made as close to 50/50 as possible.

The allocation sequence for school level randomization was send to third party not otherwise involved in the study, who, upon request from [name], would disclose the next number on the allocation sequence to [name] when she was about to inform a particular school what condition it was allocated. Since block sizes were random, it was not possible for [name] to predict the next allocation number.

Shortly after students have changed to their permanent class (start of November 2023), a school specific school class allocation list as described above will be generated for each school allocated to the intervention condition. [name] will disclose this list to each individual school principal. The random school class allocation to either the structural only condition or the structural + group MI condition will therefore be disclosed simultaneously for all school classes at a particular school. After assignment to interventions, blinding is not possible.

### Assessment of outcomes

Survey data from the students will be collected at baseline, and 2-, 6-, 9-, and 12- months post baseline. The survey-questionnaires will be digital and time for filling out the questionnaires will be allocated during school hours. Members of the research team will introduce the surveys in person and are present in the classroom during data collection to answer any questions that may arise concerning the study, the survey, or the participants’ rights. This may facilitate retention in the trial. Furthermore, the link to the survey will be open the following 1–2 days to allow students absent on the day of testing to complete the survey.

#### Primary and secondary outcomes

The primary evaluation of efficacy is based on outcomes measured 12 months post baseline.

We will examine the effect of the interventions on the following primary outcome:

Past month high intensity drinking: peak drinks per drinking event, assessed with the Timeline FollowBack (TLFB) [87].

We will examine the effect of the interventions on the following secondary outcomes:

Past month alcohol-related consequences, assessed by 21 items covering physical, social and mental issues related to hazardous use of alcohol, developed by the team for Danish youth based on previous Danish surveys and the Rutgers Alcohol Problems Index [88] e.g. black-outs, (emotional) hangovers, sexual contact that was later regretted, with yes/no response options (summed score).Past month heavy episodic drinking events assessed by TLFB (count measure).Well-being in class assessed by six items rated on a five point scale from ‘completely disagree’ to ‘completely agree’ e.g., *I feel accepted by the others in my class* (inspired by [89]) (summed score).Psychological well-being, assessed by The World Health Organization Five Well-being Index (WHO-5) [90] (summed score).Past month use of nicotine products (days using nicotine products; count measure), and past month use of illegal substances (days using cannabis, cocaine, and other illegal drugs; count measure).

### Assessment of implementation fidelity, feasibility, and acceptability

Assessment of implementation fidelity, feasibility, and acceptability will be done in the following ways:

#### School policies for school-based social events

In order to measure the degree to which the school policies for school-based social events have been implemented, all students (from intervention and control schools) will be asked to assess to which degree they experience that the different policies apply to their school. Hence, as part of the surveys students will be asked “how often do you find that the following applies at your high school” followed by e.g., (1) students below 16 can buy alcohol at the school’s parties, or (2) invitations to the schools parties encourage heavy drinking. This will be assessed at baseline, 2-, 6-, 9-, and 12 months post baseline.

#### Parent meeting

To evaluate feasibility of the interactive parent meeting, we will evaluate attendance rates. To evaluate acceptability of the parent meeting, we will examine parent satisfaction with the meeting, including whether they found the information relevant, and whether they would recommend the school to offer this meeting to parents next year (i.e., parents of first year students). These measures will be administered at the end of the parent meeting via an anonymous link.

#### Group MI

To evaluate feasibility of the group MI, we will evaluate enrollment. To evaluate acceptability of the group MI sessions, we will examine whether the students liked taking part and whether they would recommend it to other students. Furthermore, we will use open-ended questions to examine what they liked, what could be improved and what made an impression on them [67]. Acceptability measures of group MI will be administered to students in the structural + group MI condition shortly after the last group MI session.

In line with our recent pilot study of group MI for adolescents [67], researchers delivering group MI will be trained in the MI manual and practice (by [name] and an experienced external MI trainer). All sessions will be audio recorded for MI integrity and fidelity evaluation; (1) for supervision during the trial to prevent therapist drift, and (2) for post-hoc evaluation of MI integrity and fidelity by the MI Coding Lab at University of Southern Denmark. A total of 30% of all conducted sessions will be assessed, using an established metric of MI fidelity [91], similar to the procedure in our pilot trial. The fidelity of MI will be measured by means of Motivational Interviewing Treatment Integrity manual version 4.2.1 (MITI 4) [91]. MITI 4 measures 10 different behavioral counts and four global scores. The behavior counts are: *giving information, question, simple reflection, complex reflection, affirmation, seeking collaboration, emphasize autonomy, persuade with permission, persuade*, and *confront*. The four global scores are: *cultivating change talk, softening sustain talk, partnership*, and *empathy* [91]. The constructs in the MITI 4 have demonstrated acceptable interrater reliability [92].

Furthermore, we will investigate the implementation fidelity of the school, parent and student level interventions using qualitative interviews with a random sample of staff involved in the project at intervention schools (principal and relevant teachers/other staff). Interviews will be done after the last follow-up survey and will be focused on the perception of the interventions, how participation in the interventions was perceived and suggestions for improvement of the interventions.

### Data management

Quantitative data from the surveys will be entered into a SurveyXact server hosted on a secured server in Denmark. Quantitative data from the randomization, enrollment, and the surveys, audio recordings of the group MI sessions as well as qualitative data from the interviews will be kept on a secure server hosted by Aarhus University. At the end of the trial, the quantitative data will be uploaded to a server on Statistics Denmark if we deem it appropriate to merge data with national registers. The MI Coding Lab at University of Southern Denmark will code 30% of all conducted group MI sessions via a secure website: https://app-kodningslab.cloud.sdu.dk/. All audio recordings of group MI sessions will be deleted after coding and analysis. For all other data, only current and future members of the research team, who have a research affiliation to Aarhus University, will have access to the data.

### Statistical analyses

All descriptive analyses, the consent rate, the participation rate at the interactive parent meetings, the participant rate at each of the two group MI sessions, the completion rate of all surveys, and potential study drop-out will be reported and summarized after the quantitative data collection has ended. All of this information will be provided in a CONSORT flowchart.

Summaries will be presented as means and standard deviation of variables that are approximately normally distributed, or as medians and IQRs for skewed variables. Categorical variables will be summarized as frequencies and percentages.

The main objective of the statistical analyses is to assess: (a) the superiority of the structural only condition versus the control condition on hazardous alcohol use 12-months post baseline; (b) the superiority of the structural + group MI condition versus the structural only condition on hazardous alcohol use 12-months post baseline; and (c) the superiority of the structural + group MI condition versus the control condition on hazardous alcohol use 12-months post baseline.

As the primary outcome is a count measure of alcohol use, where we expect extra zeros due to students not drinking for e.g., age- or religious reasons, we plan to analyze the main objectives ideally using zero inflated generalized linear mixed models with poison family and log link-function. In case the zero inflated generalized linear mixed model cannot converge, we will instead evaluate the main objectives using a zero inflated (normal) linear mixed model. In either case, random effect will be added for intercept (i.e., clustering of longitudinal measurements within students), whereas higher order clustering will be accounted for using robust standard errors.

Secondary outcomes will be analyzed using mixed models to account for the nested data-structure. Depending on the distribution of the specific outcome either (normal) linear mixed models or generalized linear mixed models with poison family and log link-function, and potentially zero-inflated. We expect well-being measures to be somewhat normally distributed, whereas count of alcohol related consequences, count of heavy drinking episodes, and count of days using tobacco or illegal substances will somewhat follow a zero-inflated poisson distribution.

Analyses of efficacy (primary and secondary outcomes) will be based on the intention-to-treat sample, utilizing all available follow-up data from all randomized participants. All randomized participants will be analyzed within the condition they were allocated after randomization, regardless of whether they complete the intervention or not. Participants who withdraw their consent for use of their data during the trial period will not be included in any of the analyses.

No interim analyses and stopping guidelines will be applied, because the prevention interventions of the trial do not entail risk of harm to the participants.

Results from the trial will be published in international peer-reviewed journals, preferably with open access, and in national outlets with open access. Furthermore, presentations of main findings are offered to participating schools and other interested stakeholders.

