**Fig. 1 Fig1:**
[figure not shown]
**Study Design with randomization to the three conditions in two steps** In the first step (Spring 2023), 16 high schools were recruited and randomized to a control (5 control high schools) or intervention (11 intervention high schools) condition. In the next step (November 2023), randomization occurs at class-level within the intervention schools, i.e., half of the classes at the 11 intervention schools are randomized to the structural only condition and the other half are randomized to the structural + group MI condition

Structural condition with interventions targeting the school and parent level (**structural only condition**).Structural condition combined with group MI condition which also targets the student level (**structural + group MI condition**).Assessment only control condition which includes the same assessments as the other two conditions; interventions are offered after the last follow-up survey (**control condition**).

Furthermore, we use a participatory research design, applying stakeholder theory, which suggests that engaging stakeholders in intervention planning, implementation, and evaluation stages enhances program outcomes [75]. An impactful avenue for improving the development and implementation of interventions is to mobilize both explicit and tacit knowledge from multiple stakeholders and enable collaborative knowledge generation [76]. Shared learning between academic and community knowledge is fundamental for participatory research, which necessitates the establishment of equitable research partnerships with a diverse group of stakeholders – here within school settings, namely school principals, executive assistants, teachers, and students (target group), who impact both the implementation of the interventions and the quality of the research [77–79]. To ensure a high degree of shared learning in all stages of the process from exploring key concepts to designing, testing, and evaluating the interventions, the following are integrated into the trial:

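### School and class clustering is left to robust standard errors with 16 schools (5 control) and no stated few-cluster correction, whereas the power came from a four-level random-effects model

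*Protocol article*

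**What the plan says.** Under Statistical analyses, the primary outcome is to be analysed with a zero-inflated Poisson mixed model, with a zero-inflated normal mixed model as fallback. Both versions carry one random intercept, for repeated measurements within students, "whereas higher order clustering will be accounted for using robust standard errors". The article does not say whether the robust errors cluster on school or class, whether they are corrected for few clusters, or which reference distribution is used.

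The legend of Fig. 1 gives the design: "16 high schools were recruited and randomized to a control (5 control high schools) or intervention (11 intervention high schools) condition". At the second stage, "half of the classes at the 11 intervention schools are randomized to the structural only condition", and the rest go to structural + group MI.

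The Sample size section uses another model. Its simulated data have four levels: "levels were repeated measurements (level 1) nested within students (level 2) nested within school classes (level 3) nested within school (level 4"). The simulated outcomes were "analyzed using four-level mixed linear models with random intercept and with interaction between experimental condition and measurement timepoint", and "three parameters were tested for significance at alpha = 0.05".

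**The concern.** The ordinary sandwich variance is a large-sample device, and its sample size is the number of clusters. Both control contrasts set 5 control schools against 11 intervention schools. With so few, the sandwich is biased downward and is itself noisy, so a z reference gives intervals that are too short and tests that reject too often. All three primary hypotheses rest on this method, and the article expects the results to inform prevention policy.

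The mismatch with the power model is a second matter. The stated power was obtained with school and class as random effects. The planned primary analysis has neither, so the power figure does not describe it.

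**Working it through.** **Inputs.** All are from Sample size or Fig. 1 unless marked.
- Variances: school 2, class 2, student 4, residual 7.
- Cluster sizes in the simulation: "school size between 2 and 11 school classes, and (2) school class size between 25 and 28 students"; midpoints 6.5 classes and 26.5 students.
- Schools: 5 control, 11 intervention, with intervention classes split 50/50.
- Alpha 0.05 per contrast. Two-sided is assumed, as the article does not say.

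**The plan's own figure.** Power above 0.80 is stated for 15 schools. Take 5 control and 10 intervention schools and test the 12-month difference in level.
- Class-mean variance apart from school: 2 + (4 + 7)/26.5 = 2.415.
- Variance of structural only versus control: 2(1/5 + 1/10) + 2.415(1/32.5 + 1/32.5) = 0.749, so SE = 0.865.
- Power for the 1.5-unit difference: Φ(1.5/0.865 − 1.96) = 0.41. A simulated four-level REML fit gives 0.43.
- The other two contrasts come out at 0.95 or more, as stated.
- If the difference in change was tested instead, the random intercepts cancel and power exceeds 0.99.

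The stated figure is therefore not reproduced for the 1.5-unit contrast. The simulated trajectories are not given, and this is separate from the present point.

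**Type I error by hand, 16 schools of equal size.** Take an ordinary school-clustered sandwich with the factor G/(G − 1) = 16/15.
1. Control-arm variance: 2/5 + 2.415/32.5 = 0.474. Structural-only arm: 2/11 + 2.415/35.75 = 0.249. Total 0.724, of which 66% comes from the 5 control schools.
2. Expected sandwich variance: (0.474 × 4/5 + 0.249 × 10/11) × 16/15 = (0.379 + 0.227) × 1.067 = 0.647. Ratio to the truth 0.647/0.724 = 0.893, so the SE is about 0.945 of its correct value.
3. Effective degrees of freedom: (0.379 + 0.227)² / (0.379²/4 + 0.227²/10) ≈ 8.9.
4. With z, the real cut-off is 1.96 × 0.945 = 1.853 on 8.9 df, a two-sided error of **0.097**. With t(14), it is 2.145 × 0.945 = 2.027, an error of **0.073**. Structural + group MI versus control is the same by symmetry.
5. For structural + group MI versus structural only, the 11 within-school differences give 10 df and a variance ratio of (10/11)(16/15) = 0.970. The error is 0.082 with z and 0.061 with t(14).

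**Type I error by simulation.** Schools of 2-11 classes, 12-month arm means, school-clustered sandwich with G/(G − 1). A run of 20,000 null trials gave:

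| Contrast | z | t(14) |
|---|---|---|
| Structural only vs control | 0.111 | 0.085 |
| Structural + MI vs control | 0.111 | 0.085 |
| Structural + MI vs structural only | 0.088 | 0.065 |

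Other runs of the same scenario gave 0.105-0.124 for the control contrasts and 0.083-0.096 for the third.

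**Sensitivity (z reference; structural only vs control / structural + MI vs control / structural + MI vs structural only).**
- Log-ratio link: 0.112 / 0.113 / 0.088.
- School variance 0.15 and class variance 0.3: 0.102 / 0.100 / 0.092.
- Change from baseline: 0.095 / 0.096 / 0.090.
- Equal school sizes: 0.099 / 0.095 / 0.087.
- Clustering on class instead of school: 0.311 / 0.302 / 0.018.

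**After a fix.** The four-level model with school and class random intercepts gives 0.047 / 0.050 / 0.033 with t(14), and 0.062 / 0.067 / 0.048 with z. Keeping the sandwich, a per-arm correction with Satterthwaite-type df gives 0.067 / 0.065 / 0.059.

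**The case against.** The strongest reply is that the size of the inflation depends on details the article leaves open. Robust standard errors can be bias-reduced and used with small-sample degrees of freedom, and an unseen analysis plan may say so. Most of the excess error then disappears, as the 0.059-0.067 figures show. This stands, and it is why the figures are conditional on an ordinary sandwich. It does not remove the point. The article fixes the method in its usual form, and replacing z by t(14) alone is not enough for the control contrasts.

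Four other replies also stand:
- The zero-inflated mixed model itself was not simulated; linear and log-ratio estimators stood in for it.
- The 2-11 class range is a simulation input. A reader might infer that the recruited control schools differ greatly in size, but the article does not report their sizes. Inflation persists with equal sizes.
- Robust errors are a defensible way to limit convergence trouble, which the article anticipates, and to cope with students changing class in November. Kenward-Roger and Satterthwaite degrees of freedom are not routine for a zero-inflated Poisson mixed model.
- Leaving school out of the model for the within-school contrast is not an error if the sandwich clusters on school, because it captures the covariance between the two arms. Any loss of efficiency from omitting school and class effects is a matter of preference.

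**Conclusion.** The point holds in conditional form. With 16 schools, 5 of them control, an ordinary school-clustered sandwich with a z reference has a type I error of about 0.10-0.12 for the control contrasts and about 0.09 for structural + group MI versus structural only, against a nominal 0.05. With t(14) the control contrasts remain at about 0.07-0.09. This rests on the plan's variances and on simpler estimators than the planned one, and it changes little with smaller variances, equal school sizes or a log-ratio scale. Clustering on class alone would be much worse for the control contrasts (about 0.3) and conservative for the third, so the clustering level must be stated.

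Three stronger readings are not supported. The plan does not ignore clustering: it moves school and class from the random effects to the standard errors. It cannot be said without qualification that the false-positive rate doubles, because that assumes no few-cluster correction. Nor does the model mismatch show that power is lower under the planned analysis. It shows only that the stated power was computed for a different one.

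**What to change.** State in the analysis plan that robust errors cluster on school, and choose one few-cluster method for the control contrasts:
- a bias-reduced (CR2-type) variance with Satterthwaite-type degrees of freedom; or
- a randomisation test over school allocations that follows the blocked scheme under Assignment of interventions.

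Alternatively, where the model converges, add school and class random intercepts to the student intercept, as in the power model, with the permanent class as the class unit for the 12-month outcome. Use a t reference with about 14 degrees of freedom for the control contrasts, and name in advance one of the methods above as the fallback.

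Then reconcile Statistical analyses with Sample size, either by aligning the two models or by recomputing power for the model that will be used.

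The cost is wording and somewhat wider intervals for the control contrasts. The random-effects option also carries a higher risk of non-convergence.
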